# The effectiveness of kinesiology taping on dysphagia in brain tumor survivors after neurosurgery: study protocol for a pilot randomized controlled trial

**DOI:** 10.3389/fmed.2025.1571591

**Published:** 2025-10-31

**Keywords:** stroke, deglutition disorders, dysphagia, swallowing therapy, kinesiology taping, rehabilitation

## Abstract

Dysphagia is a common complication in brain tumor survivors, either as a direct symptom of the tumor or a result of neurosurgery. With improved survival rates, the need for effective rehabilitation strategies is more crucial than ever. Kinesiology taping has shown promise in dysphagia rehabilitation for stroke patients, but its potential in brain tumor survivors is largely unstudied and represents a significant research opportunity. This pilot study aims to assess feasibility and gather preliminary data on the impact of kinesiology taping, in addition to standard dysphagia care, on improving swallowing function in brain tumor survivors post-neurosurgery. This 1:1 parallel-group randomized controlled trial will recruit 62 brain tumor survivors with oropharyngeal dysphagia from a Neurosurgery Inpatient Unit in Portugal. Participants will be randomized into two groups: the control group, receiving standard dysphagia care, and the experimental group, receiving kinesiology taping applied to the suprahyoid muscles in addition to standard care. The intervention will last 15 sessions over 4 weeks. Primary outcomes will be assessed using the FEES Penetration-Aspiration Scale, Gugging Swallowing Test (GUSS), Dysphagia Handicap Index (DHI), and Functional Oral Intake Scale (FOIS). This study will evaluate the efficacy of kinesiology taping as a supplementary therapy for dysphagia rehabilitation in brain tumor survivors. The potential improvements in clinical care and patient outcomes are significant, reinforcing the importance of this research in enhancing the quality of life for these survivors.

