The use of kinesiology taping has generated positive results in a handful of early studies in rehabilitating dysphagia in stroke patients (5, 6, 19). In the pharyngeal phase of swallowing, the suprahyoid muscles are responsible for elevating and stabilizing the hyoid bone and larynx, contributing to proper swallowing mechanisms, including airway protection and opening of the upper esophageal sphincter. If the suprahyoid muscles are weak or damaged, it can result in dysphagia (20, 21). Therefore, strengthening the suprahyoid muscles can be essential to dysphagia rehabilitation to improve swallowing function and reduce the risk of complications (22). In addition, previous studies show that using kinesiology taping to strengthen the suprahyoid muscles can be an effective dysphagia rehabilitation intervention in stroke survivors (5, 6, 19). Thus, given these findings, we present the protocol of a combined intervention using dysphagia training and kinesiology tape application on brain tumor survivors. Therefore, this randomized controlled trial aims to assess the effects of kinesiology tape application in addition to usual care on dysphagia in brain tumor survivors after neurosurgery.

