Dysphagia Handicap Index (DHI). The DHI is a self-reported questionnaire designed to assess the impact of dysphagia swallowing on an individual’s daily life. It evaluates three key dimensions: physical, functional, and emotional aspects of living with dysphagia. The DHI consists of 25 items, scored using a Likert scale, with higher scores indicating a more significant perceived handicap.Functional Oral Intake Scale (FOIS). The FOIS is a clinical tool used to evaluate a patient’s ability to consume oral foods and liquids. It provides a standardized measure of functional oral intake, particularly in individuals with dysphagia. The scale consists of 7 levels, ranging from complete reliance on non-oral feeding to the ability to eat and drink without restrictions.

The secondary outcome of this study will be evaluated at T1 by the following key domains:

(1)   Recruitment (number of patients that express interest in participating);(2)   Enrollment (number of patients that participate in the program);(3)   Retention (number of sessions and percentage of enrolled participants who completed final program assessments);(4)   Satisfaction (assessed with an exit survey) will be recorded using binary response questions (yes/no) and a 5-point Likert-type scale;(5)   Adverse events that happen throughout the intervention (will be documented in the case report form).

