If kinesiology taping is effective, it could have far-reaching implications for clinical practice. Rehabilitation professionals could incorporate this technique into standard dysphagia care, potentially reducing the need for more invasive interventions. Moreover, since kinesiology taping is relatively inexpensive and non-invasive, it could be particularly beneficial in settings with limited access to specialized rehabilitation services. The ease of application and potential for home use also means that patients could continue their rehabilitation outside the clinical setting, empowering them to take a more active role in their recovery and improving long-term outcomes.

While the results will remain general due to the pilot nature of the study, it is essential to emphasize the importance of developing standardized protocols for managing neurological swallowing disorders (32, 33). Such protocols are fundamental to ensuring consistency and quality of care across different clinical settings. They support the appropriate selection and timing of assessment tools and guide the implementation of evidence-based therapeutic strategies. Moreover, standardized protocols may foster effective interdisciplinary collaboration. This comprehensive approach can enhance diagnostic accuracy, streamline intervention delivery, and improve patient outcomes. Establishing and validating these protocols in populations such as brain tumor survivors is a critical step toward reducing variability in care and optimizing the rehabilitation trajectory for individuals with complex neurological impairments.

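### The feasibility aim appears in only one of the two aim statements, and recruitment and enrollment are counts that give neither uptake among eligible patients nor a recruitment rate

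*Protocol article*

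**What the plan says.** The abstract states a two-part aim, feasibility first: "This pilot study aims to assess feasibility and gather preliminary data on the impact of kinesiology taping". Further on, the same abstract says "This study will evaluate the efficacy of kinesiology taping as a supplementary therapy for dysphagia rehabilitation". The introduction closes with a single aim that leaves feasibility out: "this randomized controlled trial aims to assess the effects of kinesiology tape application in addition to usual care on dysphagia". The Discussion limits what can be claimed: "While the results will remain general due to the pilot nature of the study".

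In section 2.8 the four clinical scales (PAS, GUSS, DHI and FOIS) are primary, and feasibility is covered by five secondary domains assigned to T1. The first two are "Recruitment (number of patients that express interest in participating") and "Enrollment (number of patients that participate in the program"). The third, retention, is defined by sessions and by the percentage of those enrolled who complete the final assessments. Satisfaction uses yes/no and 5-point items, and adverse events are recorded in the case report form.

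The recruitment target is 62 in the abstract and 80 (40 per group) in section 2.4.

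**The concern.** A reader cannot tell from the two aim statements whether feasibility is an objective of the trial or a by-product. If it is an objective, a follow-on trial would want to know what share of eligible patients accept randomisation and how many can be randomised per month in a unit of this kind. Both need a denominator or a time base, and the two measures that should supply them have neither. This is a question of how the article defines the measures, not of detail left out: the same list does give retention a denominator.

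**Working it through.** **Step 1: the aims side by side.**

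| Place | Feasibility | Effect |
|---|---|---|
| Abstract, aim | named first | preliminary data |
| Abstract, closing part | not mentioned | efficacy to be evaluated |
| Introduction, final sentence | not mentioned | effects of taping |
| Discussion | not mentioned | results limited by pilot status |

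The statements differ both on whether feasibility is an aim and on how firm the effect results will be.

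**Step 2: the five domains in section 2.8.**

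| Domain | Measure | Denominator | Time base |
|---|---|---|---|
| Recruitment | number interested | none | none |
| Enrollment | number participating | none | none |
| Retention | sessions; % completing final assessments | enrolled participants | programme |
| Satisfaction | yes/no and 5-point items | respondents (implied) | exit survey |
| Adverse events | recorded events | participants (implied) | intervention period |

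Only the first two lack what is needed.

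**Step 3: what the enrollment count can show.** Let E be the number enrolled, A the number eligible and N the target. Uptake is E/A, and E cannot exceed N. If the target is met, E = N whatever A is. The article gives no A, so the denominators below are illustrative:

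- E = 80: 80/100 = 80%; 80/400 = 20%.
- E = 62: 62/100 = 62%; 62/400 = 15.5%.

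The same count fits very different uptakes. It carries information only when it falls short of N, and the article gives two values of N.

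**Step 4: what the two counts give together.** Enrolled/interested can be derived. Patients who express interest are already self-selected, so this ratio is not uptake among eligible patients. Neither count gives a monthly rate.

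**Step 5: what retention already gives.** The plan's own step reproduces: 34/(1 − 0.15) = 40 per group, 80 in total, with 80 × 0.85 = 68 expected completers. The 34 per group is taken as stated; nothing here depends on it. The exact (Clopper-Pearson) 95% limits are the 0.025 quantile of Beta(x, n − x + 1) and the 0.975 quantile of Beta(x + 1, n − x):

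- 68/80 = 85.0%: 75.3% to 92.0%.
- 34/40 = 85.0% (one arm): 70.2% to 94.3%.
- With 62 recruited, 62 × 0.85 = 52.7. Taking 53/62 = 85.5%: 74.2% to 93.1%.

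Retention is therefore estimable with useful precision at either target.

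**Step 6: what uptake would give with a denominator.** Uptake of 30%, 50% and 70% is assumed. Wilson 95% limits are [p + z²/2n ± z√(p(1 − p)/n + z²/4n²)]/(1 + z²/n), with n the number in the denominator:

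| Enrolled | n | 95% interval |
|---|---|---|
| 80 | 267 | 24.8% to 35.7% |
| 80 | 160 | 42.3% to 57.7% |
| 80 | 114 | 61.2% to 77.8% |
| 62 | 207 | 24.1% to 36.5% |
| 62 | 124 | 41.3% to 58.7% |
| 62 | 89 | 59.5% to 78.2% |

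The half-width is roughly 5 to 9 points. Because recruitment stops at a target, n is itself random and these intervals are approximate.

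**The case against.** The strongest reply is that most of feasibility is already covered. Retention has its denominator, sessions are counted, and satisfaction and adverse events are recorded. This stands. A reader might infer that the trial cannot answer its feasibility aim, or cannot say whether the 4-week programme can be completed. The documents do not support either inference, because retention addresses completion directly.

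Second, enrollment is capped by the target rather than fixed by it, and a shortfall in a single unit would be a feasibility result. This also stands. It limits the point to what the count shows once the target is met.

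Third, the abstract's aim is dual. Clinical scales as primary outcomes serve its second half and fit the sample size (section 2.4) and the analysis (section 2.9), both built on a comparison of groups. The Discussion also tempers the efficacy wording. A reader might infer that feasibility has to be the primary outcome. That is a design preference, and the documents do not make the present ranking an error.

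Fourth, a journal article leaves detail to the full protocol. This disposes of any complaint about missing progression thresholds. It does not dispose of two definitions that the article itself states as counts, or of two published aims that differ.

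Fifth, the assignment to T1 can be read as a loose list heading, since adverse events during the intervention sit under it too. That is fair, and it affects no result. It only needs tidying when the definitions are rewritten.

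**Conclusion.** The point holds in a limited form. The aim is stated in two incompatible ways, and the efficacy wording goes further than preliminary data. Two of the five feasibility domains, recruitment and enrollment, are defined so that neither uptake among eligible patients nor a monthly rate can be obtained from them. Enrollment shows only whether the target was met, and that target is given as both 62 and 80. The other three domains remain informative, and the randomised comparison is not affected.

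The loss cannot be sized from the documents, because they give no number screened, eligible or approached. The 20% to 80% range rests on illustrative denominators, and the retention intervals assume that completion equals the planned 85%.

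**What to change.** 1. State the same dual aim in the abstract and the introduction, and describe the effect results to match, as preliminary estimates of effect rather than an evaluation of efficacy.
2. Replace the recruitment and enrollment counts with measures from a screening log: eligible/screened, randomised/eligible and randomised per month. Evaluate them at close of recruitment, not at T1, and give each proportion a 95% interval. The number expressing interest can stay as an intermediate step.
3. Report the existing retention percentage by arm as well as overall, with 95% intervals.
4. Reconcile 62 and 80, so that a shortfall can be read against one target.

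The cost is keeping a screening log, rewording, and somewhat more reporting; no extra patients or visits are needed. Ranking feasibility as primary or adding progression thresholds is optional. Re-ranking would also call for a new sample size rationale, since section 2.4 sizes the trial for an effect test.

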### 2.4 Sample size calculation

A repeated measures ANOVA with within-between interactions was chosen to evaluate the impact of the treatment on each group relative to their baseline. To achieve 80% power, with an alpha of 0.05, a medium effect size of 0.25, two groups, two measurements per group, a correlation of 0.5 among repeated measures, and a non-sphericity correction of 1, we used GPower v.3.1 (24) to calculate the required sample size, which resulted in 34 subjects per group. Considering a 15% dropout rate, the final sample will consist of 80 individuals (*n* = 40 per group) who meet the inclusion criteria.

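### The abstract gives a recruitment target of 62 and section 2.4 gives 80; nothing derives 62 or reconciles the two

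*Protocol article*

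**What the plan says.** The protocol article gives its sample size in two places.

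- Abstract: "This 1:1 parallel-group randomized controlled trial will recruit 62 brain tumor survivors with oropharyngeal dysphagia". At 1:1 allocation that is 31 per group. The abstract gives no derivation and no power.
- Section 2.4: the calculation, "which resulted in 34 subjects per group", is then raised for 15% dropout, so that "the final sample will consist of 80 individuals", 40 in each group.

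Section 2.4 lists its inputs. The test: "A repeated measures ANOVA with within-between interactions was chosen". The error rates: "To achieve 80% power, with an alpha of 0.05". The effect and layout: "a medium effect size of 0.25, two groups, two measurements per group". The remaining settings: "a correlation of 0.5 among repeated measures, and a non-sphericity correction of 1". Section 3.1 repeats the 15% dropout assumption. The number 62 appears only in the abstract.

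**The concern.** The number to be randomised is a basic pre-specified quantity, and here it has two values 18 apart. The usual innocent explanations fail. The figure 62 is not section 2.4's evaluable number, which is 68 (2 × 34). It is not what remains of 80 after dropout, which is also 68. Nor is it a count of completers, because the abstract presents it as the number to be recruited. It is lower than the number section 2.4 asks for before any dropout is allowed.

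At stake is whether a reader, an ethics committee or the trial team can tell how large the trial is meant to be, and which power statement belongs to that size. Recruitment, enrolment and retention are themselves listed outcomes in section 2.8, and they are hard to interpret against an ambiguous target.

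**Working it through.** **Inputs.** From section 2.4: effect size f = 0.25, alpha = 0.05, power 80%, k = 2 groups, m = 2 measurements, correlation ρ = 0.5, non-sphericity correction ε = 1, dropout 15%. Targets: 62 (abstract) and 80 (section 2.4).

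**Step 1: section 2.4's dropout step.** 34 × 2 = 68, and 68 / (1 − 0.15) = 80. This reproduces, so 80 follows from 34 per group.

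**Step 2: evaluable numbers under each target.**
- 80 × 0.85 = 68, or 34 per group.
- 62 × 0.85 = 52.7, so 52 to 53 in total, about 26 per group.
- Before any dropout, 62 is already 68 − 62 = 6 short of the stated requirement.

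**Step 3: section 2.4's 34.** For the within-between interaction, with the effect-size definition that uses the correlation, the test statistic is noncentral F with
- noncentrality λ = N × m × f² × ε / (1 − ρ) = N × 2 × 0.0625 / 0.5 = 0.25 N,
- df1 = (k − 1)(m − 1)ε = 1,
- df2 = (N − k)(m − 1)ε = N − 2,

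where N is the total over both groups. The smallest even N with at least 80% power is 34 (λ = 8.5, power 0.807). That is 34 in total, 17 per group. Section 2.4 labels the same number as per group, so its 68 is not reproduced.

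Alternatives do not give 68 at 80% power either. The between-groups test needs 98, and two other effect-size definitions, which do not use a correlation, need 128 and 130. Keeping the interaction test but setting ρ to 0 gives 66.

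**Step 4: power at each size, on section 2.4's inputs.**

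| Target | Evaluable N | λ = 0.25 N | Power |
|---|---|---|---|
| 62, 15% dropout | 52 | 13.0 | 0.942 |
| 62, 15% dropout | 53 | 13.25 | 0.946 |
| 62, no dropout | 62 | 15.5 | 0.972 |
| 80, 15% dropout | 68 | 17.0 | 0.982 |
| 80, no dropout | 80 | 20.0 | 0.993 |

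After dropout the two targets differ by about 4 percentage points of power, and both exceed 80%.

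**Step 5: where 62 might come from.** It does not follow from the stated inputs. The same formula at 95% power gives N = 54, and 54 × 1.15 = 62.1, so the figure could be left over from a different calculation. That is inference; the article does not say so.

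**The case against.** The strongest reply is that section 2.4 is the dedicated section. It shows a derivation, its dropout step works, and section 3.1 repeats the 15%. The abstract's 62 stands alone and may simply be out of date, so a sensible reader would take 80. The article also calls the study a pilot, for which a modest discrepancy in size might seem harmless. The plausibility of a stale abstract figure stands, but it does not remove the contradiction. Because section 2.4's 34 per group cannot be reproduced, 80 cannot be taken as correct by default. Pilot status does not help either, since section 2.4 makes a formal power calculation.

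A reader might make two stronger inferences that the article does not support.

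- *That recruiting 62 leaves the trial underpowered.* It falls short only of the stated 34 per group. On section 2.4's own inputs, 52 evaluable participants still give about 0.94. Showing low power would require an effect smaller than the f = 0.25 planned for, and the article names no such effect.
- *That two targets would let the team choose when to stop after seeing results.* No interim look is described, and section 2.5 blinds the person collecting and analysing the data to allocation, although participants and treating clinicians are not blinded. That inference is conjecture.

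**Conclusion.** The contradiction stands: 62 and 80 cannot both be the recruitment target, and the article offers nothing to reconcile them. Taken with 15% dropout, 62 yields about 52 to 53 evaluable participants against the 68 that section 2.4 says it requires.

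The consequence is a mis-stated plan, not a demonstrated loss of power. The article states only one power, 80%, and it belongs to section 2.4; the 0.94 and 0.98 are implied by the two sizes. These values assume the effect-size definition that uses the correlation. The article does not name the definition, but it does state a correlation, which the two alternative definitions tried do not use. Changing the abstract to 80 would remove the conflict and still leave section 2.4's own number unreproduced.

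**What to change.** 1. Confirm the intended number to be randomised and state it identically in the abstract and section 2.4.
2. State in section 2.4 whether 34 is the total or the number per group. If it is the total, the dropout step gives 34 / 0.85 = 40 randomised in all, and a larger target needs its own justification. If 34 per group is intended, the 80% power statement does not match the listed inputs, and either the power or the input that differs should be corrected.
3. Give the power for the chosen number after dropout: on the present inputs, about 0.94 for 62 and 0.98 for 80. Name the effect-size definition used.

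The cost is a few words in two places and one rerun of the calculation, with no change to the design unless the sponsor decides on a different size. The flowchart image and the registry record were not available, so no error is claimed there; the sponsor should check that they carry the same number.

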### 2.8 Data collection

We will use the participants’ clinical records to collect the following characteristics: Participants’ sex, age, educational level, occupation, brain tumor history, and comorbidities.

A blinded researcher will assess primary study outcomes at baseline *T0* and after intervention *T1* (until 24 h after the final session).

The following domains will assess the primary outcomes of this study:

The Fiberoptic Endoscopic Evaluation of Swallowing (FEES) will be used alongside the Penetration-Aspiration Scale (PAS). Participants will be asked to swallow solid, semi-liquid, and liquid food. The assessment will be stopped if aspiration occurs, defined as the entry of food into the airway below the true vocal cords (26). The PAS is an 8-point scale that evaluates the severity of food or liquid entering the airway during swallowing, based on FEES observations. It assesses how far the material penetrates and whether it is cleared. Scores range from no airway entry to material entering below the vocal cords, not being cleared, and no protective response (silent aspiration).Gugging Swallowing Test (GUSS). The GUSS is a clinical tool used to assess the safety of swallowing in patients and identify the risk of aspiration. The test evaluates the patient’s ability to swallow different food and liquid consistencies, beginning with thickened fluids and gradually progressing to thin liquids. The GUSS is divided into two main parts: the indirect swallowing test, which assesses the patient’s ability to swallow saliva and checks for symptoms of dysphagia, such as coughing or drooling, and the direct swallowing test, which observes for signs of aspiration or choking as the patient is given substances of increasing difficulty (semisolid, liquid, and solid).

The maximum score indicates safe swallowing without aspiration risk, while lower scores suggest higher aspiration risk.

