### 2.9 Data analysis

Descriptive statistics measures of mean, standard deviation, median, minimum, maximum, and range will be used to characterize the sample in terms of sociodemographic characteristics and variables of interest for each group in the study. In addition, boxplots will also be created to show these variables in a graphical format. Subsequently, a repeated measures analysis of variance (ANOVA) will be used to identify the differences between the two groups and evaluate which exhibits better outcomes. The assumptions of the ANOVA will be verified through the Mauchly’s test of sphericity, the Levene test for homogeneity of variances and visual observation of the Q-Q plot.

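### Four unranked primary outcomes, one power calculation tied to none of them, and no rule for what counts as success

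*Protocol article*

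**What the plan says.** All references are to the protocol article.

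- **Abstract:** "Primary outcomes will be assessed using the FEES Penetration-Aspiration Scale, Gugging Swallowing Test (GUSS), Dysphagia Handicap Index (DHI), and Functional Oral Intake Scale (FOIS"). The Abstract calls the study a pilot for feasibility and preliminary data, and then says it will evaluate the efficacy of taping.
- **Section 2.8 (Data collection):** "The following domains will assess the primary outcomes of this study". The same four instruments follow, and none is put first. The feasibility measures (recruitment, enrollment, retention, satisfaction, adverse events) are the secondary outcome.
- **Section 2.4 (Sample size calculation)** gives its reason for the test: "A repeated measures ANOVA with within-between interactions was chosen to evaluate the impact of the treatment on each group relative to their baseline". The inputs are "To achieve 80% power, with an alpha of 0.05, a medium effect size of 0.25, two groups, two measurements per group", with "a correlation of 0.5 among repeated measures, and a non-sphericity correction of 1". The section names no instrument. It arrives at 34 per group, and at 80 in total after 15% dropout.
- **Section 2.9 (Data analysis):** a repeated measures ANOVA "will be used to identify the differences between the two groups and evaluate which exhibits better outcomes". The section states no significance level, no order among the four outcomes and no rule for combining them.

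**The concern.** The primary outcome and the sample size should describe the same decision. Here the sample size describes one test of one unnamed variable, while the trial will produce four primary results. Nothing says whether success means one positive scale, all four, or something between.

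The choice matters because the rules behave differently. If any one scale is enough, the chance of a false claim is larger than the alpha in section 2.4. If all four are needed, the chance of a false claim is at most that alpha, but the chance of a true claim is lower than the single-test power. A rule chosen after the results are known would have no defined error rate. The Discussion sets out practice implications should taping prove effective, so a reader needs to know in advance which result would support that statement.

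**Working it through.** **Inputs.** From section 2.4: alpha 0.05, power 80%, f = 0.25, two groups, two measurements, correlation 0.5 between repeated measures, non-sphericity correction 1. From the Abstract and section 2.8: four primary outcomes. The correlation between the four test statistics is not in the document; I assumed values from 0 to 0.9.

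**1. The plan's own figure.** For the within-between interaction, λ = f² × N × m / (1 − ρ), with 1 and N − 2 degrees of freedom.

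- N = 34 in total: λ = 0.0625 × 34 × 2 / 0.5 = 8.5, power 80.7%.
- N = 68 in total: λ = 17, power 98.2%.

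The stated inputs therefore give 34 in total, not 34 per group. The dropout step reproduces: 34 / 0.85 = 40 per group, 80 in total. The per-group reading, and the 62 in the Abstract against the 80 in section 2.4, are separate matters. Here they mean only that power has to be shown at several values of N.

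**2. Any one of four counts, each at two-sided 0.05.**

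- Independent: 1 − 0.95⁴ = 18.5%. Upper bound whatever the correlation: 4 × 0.05 = 20%.
- Correlated, by simulation of equicorrelated normal statistics (1,000,000 draws):

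| Assumed correlation | At least one false positive |
|---|---|
| 0.3 | 17.4% |
| 0.5 | 15.6% |
| 0.7 | 13.0% |
| 0.9 | 9.4% |

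These rates count false results in either direction. For results favouring taping only, the independent case is 1 − 0.975⁴ = 9.6%, against 2.5% for one test.

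**3. All four required.** The type I error is at most 5%. If each test had the 80% power named in section 2.4, joint power would be 0.80⁴ = 41% for independent scales, and could lie anywhere from 1 − 4 × 0.20 = 20% up to 80%. If f = 0.25 held on every scale with 68 evaluable, joint power would be at least 1 − 4 × (1 − 0.982) = 92.8%. Section 2.4 gives neither figure.

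**4. Cost of adjustment.** Holm's strictest step is 0.05 / 4 = 0.0125. With the same λ:

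| Evaluable N | λ | Power at 0.0125 |
|---|---|---|
| 48 | 12 | 80% reached |
| 52 | 13 | 84% |
| 62 | 15.5 | 91% |
| 68 | 17 | 94% |
| 80 | 20 | 97% |

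The row for 52 covers the smallest reading: 62 recruited less 15% is 62 × 0.85 = 52.7. On the difference-in-change scale, f = 0.25 is 4 × 0.25 = 1.0 SD. With 68 evaluable, the difference detectable with 80% power rises from 0.69 SD at 0.05 to 0.83 SD at 0.0125. Both are below the planned effect.

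**The case against.** **The analysis plan may deal with it.** A multiplicity procedure can sit in a statistical analysis plan, and this article is condensed, so silence on the procedure alone would be no finding. Naming the primary outcome and sizing the trial for it is different: it is a protocol decision, and this document has made it, with four co-equal primaries against a single-test calculation. That part stands.

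**It is a pilot.** The title and Abstract say so, and the Discussion says results will remain general for that reason. This lowers the severity. It does not remove the point, because the Abstract also claims an efficacy evaluation, feasibility is the secondary outcome, and section 2.4 is a hypothesis-test power calculation.

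**The false-positive rate is not necessarily inflated.** This is right. A reader might infer that the trial tests each scale at 0.05 and will claim success on any one. Alpha appears only in section 2.4, and no section states that rule. The rates in step 2 are therefore conditional.

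**PAS might add further tests.** A reader might infer from "Participants will be asked to swallow solid, semi-liquid, and liquid food. The assessment will be stopped if aspiration occurs" that PAS is analysed separately for three consistencies, and that participants who aspirate would drop out of those analyses. The document does not say so. It describes PAS as a single 8-point scale and is silent on how the swallows become one score, which a condensed article may leave to the full protocol. I make no claim of extra tests or of lost participants.

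**Adjustment would weaken the trial.** On the stated inputs it would not, as step 4 shows.

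**Conclusion.** The point holds in a conditional form. Four unranked primaries, a single-test sample size linked to none of them and no success rule leave the trial's central decision undefined. Under an any-one rule at 0.05, the two-sided false-positive rate is roughly 9% to 19% over assumed correlations of 0.9 down to 0. Under an all-four rule the type I error is safe, and the gap is in the stated power. Under neither rule does section 2.4 describe the decision.

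The documents do not support saying that the error rate is inflated outright, nor that more participants are needed. The statement that adjustment is affordable rests on f = 0.25 and correlation 0.5 holding for each scale tested, which the document assumes but ties to no instrument. Severity: should-fix, given the pilot label.

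**What to change.** Settle one of the following before any data are seen.

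1. **One primary outcome.** Name it in the Abstract and section 2.8, tie section 2.4 to that scale, and make the other three secondary. PAS at T1 is one example. If it is chosen, define one score per participant that stays defined when the examination stops for aspiration. The choice of scale and of summary score belongs to the investigators.
2. **Four primary outcomes.** State in section 2.9 that a significant result on any one scale after Holm adjustment across the four counts as success, and restate the power in section 2.4 at 0.0125.

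The cost is wording in the Abstract and sections 2.4, 2.8 and 2.9, with the registration brought into line if it carries the same wording (it is not shown here). No extra participants are needed on the stated inputs. The downside is that, under the first option, a single non-primary scale can no longer carry the efficacy claim; under the second, a scale significant only at an unadjusted 0.05 cannot carry it.
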